### Questionnaires & follow-up

3.9

Participants will complete a series of validated questionnaires at baseline including the Patient Health Questionnaire – 9 Item (PHQ-9), Sheehan Disability Scale (SDS), Quick Inventory of Depressive Symptoms (QIDS), Assessment of Quality of Life (AQoL-8D), and a demographic questionnaire. The PHQ-9 and QIDS questionnaire will be used to assess depressive symptoms and the AQoL-8D questionnaire will assess the participants’ quality of life. These three questionnaires provide insight into the participant’s mental status and perceived quality of life in the context of their depression. Additionally, the SDS will be used to assess the patient’s functional impairment for the clinician group assessment during baseline. During the program, participants will complete the PHQ-9 every 3 weeks (i.e., weeks 4, 7, 10, and 13), and the QIDS and AQoL-8D at weeks 7 and 13. All questionnaires (i.e., PHQ-9, QIDS, and AQoL-8D questionnaires) will be filled at the 3, 6, and 12-month follow-up periods to measure post-study outcomes.

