### Sample size determination

3.10

In our previous clinical trials and gathered data (47), the average PHQ-9 score changed from 16.2 before e-CBT to 11.48 after 12 sessions of e-CBT (joint standard deviation; SD = 5.45). Based on these numbers, the effect size (Hedges’ G) is equal to 0.86. Given the effect size and a power of 0.8, we would need 14 participants to observe a significant effect in a paired sample *t*-test. Considering the completion rate of 45%, we would require 31 participants in each group to observe significant results. Given the two treatment arms and three treatment intensities, we would require 186 participants to detect significant clinical change across all groups. We believe this sample size is large enough to perform further analyses on factors such as the role of sex and gender in treatment efficacy and completion rate.

To follow up on this sample size determination, we will use previously collected data as mentioned above to simulate the population and use a random sampling method to determine the effect size for our power calculation. We will do this by simulating a population based on the mean and standard deviation of our previous e-CBT studies and collecting data, then randomly sampling participants to each treatment arm. This simulation will be developed using Python code. Based on this random sampling, we will calculate the effect size, set the power of 0.8, and consider the completion rate of 45% to determine the sample size required to detect a significant clinical change across the groups.

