## Statistical analysis

4

Initially, all data will be examined for missing, nonsensical, and outlying variables. Missing data will not be attributed and will be treated as missing. All statistical analyses will be performed at the end of the trial and will consider a significance level of 0.05 and 95% confidence intervals. Analyses will be conducted to account for and assess differences across sex and gender identifications, and how these factors affect the adaptability and efficacy of e-CBT.

### Hypothesis 1: outcomes in depressive symptoms of treatment arm 1 will be comparable to treatment arms 2 and 3

4.1

Clinical outcomes of the healthcare teams’ decision (arm 1) versus the AI’s decision (arm 2), will be compared by assessing the treatment completion rate, number of completed sessions, and change in questionnaire scores. The completion rate across the two study arms and three levels of care will be calculated using a 2 × 3 × 2 contingency matrix (i.e., healthcare team vs. AI × 3 different treatment intensities × completers vs. dropouts) and chi-square analysis to compare within and between completion rates in the two arms. We will use a 2 × 3 (i.e., healthcare team vs. AI × 3 different levels of care) two-way analysis of variance (ANOVA) to compare the number of completed sessions across participant groups and care levels. Questionnaires are collected at 3 different times; at the start (for all participants), midway (for those who completed at least 6 sessions), and end of the study (for those who completed the treatment program). We will use a 2 × 3 × 3 (i.e., healthcare team vs. AI × 3 different levels of care × 3 time points) linear mixed-effects model for each questionnaire to compare clinical outcomes within and between groups and times. A mixed-effects model analysis will account for any missing data caused by participant dropout. Finally, we will assess if demographic covariables affect clinical outcomes using multiple 2 × 2 × 3 × 3 (demographic factors (e.g., male vs. female) × healthcare team vs. AI × 3 different levels of care × 3-time points for the questionnaire’s score) mixed-effects model to account for each demographic variable (i.e., sex, gender, age, and income). Bonferroni corrections will follow the ANOVA analyses in *post hoc* analyses.

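### Section 4.1 ties midpoint and end-of-study questionnaires to sessions completed, contradicting section 3.9, and wrongly says that a mixed model deals with whatever dropout leaves missing

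*Protocol article*

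**What the plan says.** Two sections of the protocol article describe who is measured and when, and they differ.

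- **Section 3.9 (Questionnaires & follow-up)** sets a calendar: "participants will complete the PHQ-9 every 3 weeks (i.e., weeks 4, 7, 10, and 13"), with QIDS and AQoL-8D at weeks 7 and 13, and all three instruments again at 3, 6 and 12 months. It sets no condition on sessions completed.
- **Section 4.1 (Hypothesis 1)** says questionnaires are collected at three times: the start for everyone, then "midway (for those who completed at least 6 sessions), and end of the study (for those who completed the treatment program". These three times are the time factor in the 2 × 3 × 3 linear mixed model for each questionnaire.

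On missing data, the opening of section 4 says that missing values stay missing. Section 4.1 adds: "A mixed-effects model analysis will account for any missing data caused by participant dropout".

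Section 2 defines the primary objective as change in PHQ-9, QIDS and AQoL-8D from the start to the end of the 13-session programme. The introduction says the algorithm sets care intensity from the probability of dropping out. Section 4.1 also compares completion rate and sessions completed between arms. Section 3.10 plans on 45% completion.

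**The concern.** Read literally, 4.1 makes the end-of-treatment score available only in people who finished. Completion happens after randomisation, is what the triage tries to change, and is one of the outcomes compared. Selecting symptom scores on it gives up part of the protection of randomisation, and it loads the pre-post estimate of the stratified model, which is part of the primary objective, towards those who did well enough to stay.

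The mixed model is offered as the remedy. A likelihood-based mixed model gives valid estimates when missingness depends only on scores already in the model. It does not do so for missingness of every kind. Someone who leaves before session 6 brings only a baseline to the three-time model, so nothing observed shows how that person fared on treatment. The PHQ-9 scores scheduled at weeks 4 and 10, which might show it, have no place in the model.

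At stake are the size of the reported improvement and how safely similar results in the two arms can be read as comparability.

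**Working it through.** **Inputs.** Section 3.10: "the average PHQ-9 score changed from 16.2 before e-CBT to 11.48 after 12 sessions of e-CBT", SD 5.45; "Given the effect size and a power of 0.8, we would need 14 participants"; "Considering the completion rate of 45%, we would require 31 participants in each group"; 186 in total. Section 3.3: 93 per arm. Section 4: the plan "will consider a significance level of 0.05 and 95% confidence intervals"; two-sided testing is assumed here.

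**1. The plan's own figures.** Change = 16.2 − 11.48 = 4.72. Effect size = 4.72 / 5.45 = 0.866 (stated 0.86). A paired t-test at two-sided 0.05 has power 81.2% with 13 and 84.5% with 14, so 14 is adequate. 14 / 0.45 = 31.1, stated as 31, and 31 × 6 = 186. The arithmetic reproduces to within rounding. It also shows that the sample size counts only completers as evaluable, which agrees with 4.1 and not with 3.9.

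**2. End scores under the 4.1 rule.**
- With a score: 0.45 × 186 = 83.7, about 84 (42 per arm).
- Without: 0.55 × 186 = 102.3, about 102 (55%).
- Check against the earlier e-CBT-only sample in section 3.3.2: (33 + 41 + 10) / 190 = 84 / 190 = 44.2% completed. Applied to 186, about 104 (56%) would have no end score.
- The missing share falls below half only if completion exceeds 50%. At the 53.2% (33/62) seen in the subgroup judged suitable for e-CBT only, about 87 (47%) would have none.
- The number without a midpoint score cannot be worked out, because no rate of reaching session 6 is given.

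**3. Illustration for the pre-post change.** Assume that completers improve by 4.72 and non-completers by x. The true mean change is 0.45 × 4.72 + 0.55 × x.

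| x (assumed) | True mean change | Shortfall from 4.72 |
|---|---|---|
| 0 | 2.12 | 2.60 |
| 2.36 (half) | 2.12 + 1.30 = 3.42 | 1.30 |
| 4.72 | 4.72 | 0 |

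The planned model is not a completer-only analysis, so the case x = 0 was simulated with a likelihood-based three-time model under the 4.1 rule. Completers were half-improved (2.36) at the midpoint, within-person correlation was 0.3 to 0.7, and 30% to 100% of dropout fell before session 6. The model reported a change of 4.3 to 4.7 against a true 2.12. The midpoint scores of later dropouts pull the estimate down only slightly.

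**4. Precision of the arm comparison (unadjusted, SD 5.45).**
- 42 per arm: SE = 5.45 × √(2/42) = 1.19; detectable difference at 80% power about 3.3 points.
- 93 per arm: SE = 5.45 × √(2/93) = 0.80; detectable difference about 2.2 points.
- The ratio √(93/42) = 1.49 is an upper bound on the loss. The first line ignores midpoint information and the second assumes full retention.

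**The case against.** **The parentheses in 4.1 may describe rather than prescribe.** They could mean who is expected to reach each point, with 3.9 governing collection. Section 3.3.2 gives this some support: of 28 earlier participants 10 completed, yet 11 had a final PHQ-9 above 14, so at least one non-completer had some final score, possibly a last available one. This stands in part. A loss of 102 end scores is what follows if 4.1 is applied, not a proven outcome. The contradiction remains either way.

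**Non-completers are not excluded.** All participants enter at baseline, and those with at least 6 sessions add a midpoint. This stands. A reader might infer that over half the sample has no primary outcome data at all, but the text supports only that they lack an end-of-treatment score.

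**An effect on dropout would still be seen**, because completion and sessions are compared between arms. True, but it would not be reflected in the symptom estimate.

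**A three-time model is coherent across instruments**, since QIDS and AQoL-8D are scheduled only at baseline and weeks 7 and 13. That is a fair reason for those two. It is not a reason to leave out PHQ-9 scores that 3.9 schedules.

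**Missing-data assumptions belong in an analysis plan.** Usually so, and their absence would be no finding. Here the article makes a positive claim that is too broad, and states a collection rule that creates the missingness.

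**Reduced numbers were planned for** through the 45% inflation. That covers the number of end scores, not their selection.

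**Conclusion.** The point holds as a contradiction between 3.9 and 4.1, together with an incorrect statement about the mixed model. Under 4.1 at 45% completion, about 102 of 186 (55%) would have no end-of-treatment score, selected by an outcome of the trial, and early dropouts would contribute only a baseline.

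The possible overstatement of mean improvement is large if non-completers do not change (2.12 true against 4.3 to 4.7 reported), and it shrinks to nothing as their change approaches that of completers. The documents do not say where between these the truth lies, and using 4.72 as the completers' change is itself an assumption.

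Two stronger readings are not supported. A reader might take the 53% and 36% completion rates in section 3.3.2 and infer a hidden arm difference of (0.532 − 0.357) × 4.72 = 0.83 points. Those rates belong to the algorithm's suitability strata, all treated with e-CBT only; they are not trial arms, and no difference in completion between arms can be predicted from the article. A reader might also infer that intervals will be 49% wider than they need be; that is a ceiling, since no fix secures scores from all 93 per arm.

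**What to change.** 1. In section 4.1, delete the two session-based conditions so that it agrees with 3.9. Seek the scheduled questionnaires from every randomised participant, whatever number of sessions was completed, for all time points still to come.
2. Analyse all randomised participants in the arm to which they were assigned.
3. Fit the PHQ-9 model to all five scheduled times (baseline, weeks 4, 7, 10 and 13). QIDS and AQoL-8D keep their three.
4. Replace the sentence on dropout with a statement that the model assumes data are missing at random given the modelled scores. Add one sensitivity analysis in which the unobserved scores of non-completers are shifted to be worse.

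The cost is some effort to follow up people who have stopped the programme, plus modest extra analysis. The article does not describe how questionnaires are prompted, so that effort cannot be priced from it. Full retention is not guaranteed. Recruitment began in December 2022, so scores never sought from earlier enrolees cannot be recovered; for them only the analysis changes help.

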### Participants

3.1

Participants (*n* = 186: *n* = 31 per e-CBT group * 2 arms) will be recruited at Queen’s University from outpatient psychiatry clinics at both Kingston Health Sciences Centre sites (Hotel Dieu Hospital and Kingston General Hospital), as well as Providence Care Hospital in Kingston, Ontario. Additionally, self-referrals and referrals from family doctors, physicians, and clinicians across Ontario will be accepted. After obtaining informed consent from the participant, the participant will be evaluated using the Mini International Psychiatric Assessment (MINI) through a secure video appointment to confirm a diagnosis of MDD using the Diagnostic and Statistical Manual of Mental Disorders, Fifth Edition (DSM-5) (41), by a trained professional on the research team.

All eligible participants will be randomized to receive a treatment plan based on the decision of either the healthcare team (Arm 1) or the Triage Module using an AI algorithm (Arm 2). Participants will be randomly allocated to one of the two arms of the study by a research assistant on the team who will also balance the group based on demographic variables (i.e., sex, gender, age, and income). Participants and therapists in the study will be blinded to which treatment arm the participant belongs to. By the nature of this study, participants and therapists will not be blinded to which treatment intensity the participant will receive since it will be evident whether the participant is receiving a phone/video call in addition to usual e-CBT care or pharmacotherapy. Each participant will be provided with an effective form of treatment (i.e., e-CBT) regardless of which group they will be allocated to. Participants will be informed that there is no incentive to join the program and that joining or withdrawing at any point will not affect them negatively. It will also be explained to the participants that the program is not a crisis resource and that they will not always have access to their therapists. In the case of an emergency, participants will be directed to proper resources, and this event will be reported to the study’s lead psychiatrist (principal investigator). All data will be anonymized and analyzed by research team members who are not directly involved in the patient’s care.

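### Section 4.1 models the baseline score as one of three outcome time points, so the AI-versus-team contrast is less precise than the collected data allow

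*Protocol article*

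**What the plan says.** Section 4.1 (Hypothesis 1) lists three questionnaire times: the start, for everyone; midway, for those with at least six sessions; and the end, for those who complete the programme. It then specifies the analysis of each questionnaire: "We will use a 2 × 3 × 3 (i.e., healthcare team vs. AI × 3 different levels of care × 3 time points) linear mixed-effects model". No baseline covariate and no common baseline mean is mentioned.

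The baseline scores are collected. Section 3.9 says: "Participants will complete a series of validated questionnaires at baseline including the Patient Health Questionnaire – 9 Item (PHQ-9"), and the same list includes QIDS and AQoL-8D. Section 2 makes the change in these scores, AI against healthcare team, the primary objective, with the hypothesis that the arms are comparable.

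On demographics, Section 3.1 has allocation done by a research assistant "who will also balance the group based on demographic variables (i.e., sex, gender, age, and income"). The main model contains none of these factors. Section 4.1 brings them in afterwards, one at a time, each in a separate four-way "mixed-effects model to account for each demographic variable (i.e., sex, gender, age, and income").

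**The concern.** Baseline is measured before the arm's care decision takes effect, so any baseline difference between the randomised arms is chance. A model with a free baseline mean in each arm subtracts the whole of that chance difference from the end-of-treatment difference. A baseline-adjusted model subtracts only the part that predicts the end score. The first is valid but noisier.

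At stake is the precision of the one comparison that randomisation protects. Because the aim is comparability, the cost shows first as a wider confidence interval for the arm difference, and second as lower power. The article also does not say which term of the model answers the AI-versus-team question.

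**Working it through.** **Inputs from the article.** Section 4 "will consider a significance level of 0.05 and 95% confidence intervals"; two-sided testing is assumed. Section 3.10 gives a "joint standard deviation; SD = 5.45" and 45% completion. Section 3.3 gives 93 per arm. So n = 93 baselines and nc = 0.45 × 93 ≈ 42 end scores per arm.

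**The plan's own figure.** Section 3.10 reports that "the average PHQ-9 score changed from 16.2 before e-CBT to 11.48 after 12 sessions of e-CBT", and concludes: "Given the effect size and a power of 0.8, we would need 14 participants to observe a significant effect in a paired sample" *t*-test. Here 4.72/5.45 = 0.866, against the stated 0.86. An exact paired test needs 13 participants (power 0.812), and 14 gives 0.844. Then 14/0.45 = 31.1, and 31 × 6 = 186. The figure reproduces, but it powers a within-group change. No power, difference or margin is stated for AI against team.

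**Assumption.** No pre/post correlation ρ is stated. If 5.45 is both the SD of a score and the SD of change, then 2·SD²·(1 − ρ) = SD², so ρ = 0.5. The range shown is 0.3 to 0.7.

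**Formulas** for the end-of-treatment arm difference (equal SD at both times, midpoint and care level left out):

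- Free baseline mean in each arm: Var = 2·SD²·[(1 − ρ²)/nc + (1 − ρ)²/n]
- Common baseline mean, or baseline as covariate: Var = 2·SD²·(1 − ρ²)/nc

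The second is smaller for every ρ below 1, so the direction of the finding does not depend on the assumed correlation.

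**Worked case, ρ = 0.5, 45% completion.** 2·SD² = 59.405.

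- Free: 59.405 × (0.75/42 + 0.25/93) = 1.220, SE 1.105
- Adjusted: 59.405 × 0.75/42 = 1.061, SE 1.030
- SE ratio 1.073; variance ratio 1.15
- 95% interval half-width: 1.96 × 1.105 = 2.17 against 1.96 × 1.030 = 2.02 points

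**Power after adjustment**, at the difference for which the stated contrast has 80%: Φ(2.80 × SE_free/SE_adjusted − 1.96).

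| ρ | SE free / adjusted, 42 of 93 end scores | Power | SE free / adjusted, complete data | Power |
|---|---|---|---|---|
| 0.3 | 1.265 / 1.135 | 87.8% | 0.946 / 0.762 | 93.5% |
| 0.5 | 1.105 / 1.030 | 85.2% | 0.799 / 0.692 | 89.9% |
| 0.7 | 0.883 / 0.849 | 82.9% | 0.619 / 0.571 | 86.0% |

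Adding a midpoint score for an assumed 65% of participants, with equal correlations between times, gives SE 1.090 against 1.014 at ρ = 0.5 and again about 85% power.

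**Balancing factors.** Section 3.3.2 reports p = 0.20, 0.46 and 0.39 for age, sex and income against PHQ-9 change in 190 earlier participants. Those values correspond to roughly 1.6% of the change-score variance in total, worth about half a point of power.

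**The case against.** The strongest reply is that the stated analysis is valid, that the loss is modest, and that an article may leave covariates to an analysis plan. The first two stand. The third does not fully answer the point, because the article does not leave the model open: it fixes the factors and makes the start score a response.

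A second objection also stands in part. The calculation is for a two-arm contrast, whereas the stated model crosses arm with care level. Care level is set after randomisation, by a different rule in each arm, and in Arm 2 partly from PHQ-9 (Section 3.3.2). Equality of baseline means holds for the whole randomised arms and not within care levels. The figures therefore describe the whole-arm contrast, and the fix has to say that care level is left out of it.

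Three stronger readings are tempting and are not supported:

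- **A loss of up to 10 points of power.** At ρ = 0.5 that needs end scores from everyone. Section 4.1 collects them from completers, and Section 3.10 plans on 45% completion.
- **The omitted balancing factors as a cause of the loss.** Their expected contribution is negligible on the article's own data, and they do appear in later models.
- **A test of the arm main effect, averaged over all three times including baseline.** Such a test would be much weaker: about 40% power for a difference detected with 80% by the stated contrast, with complete data, ρ = 0.5 and an effect building up as none, half, full. But the article never names that test, and its reference to change in questionnaire scores points to the arm-by-time contrast.

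**Conclusion.** The point holds as a matter of efficiency, not of bias. Under the plan's own completion rate the standard error is about 7% too large at ρ = 0.5. That is the same as needing about 15% more participants for equal precision. The power recovered from a base of 80% is about 5 points at ρ = 0.5, 3 at 0.7 and 8 at 0.3. With complete data and ρ = 0.5 it would be about 10.

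These sizes rest on an SD of 5.45 at both times, 93 per arm, an assumed correlation and a whole-arm contrast. The 80% starting point is a yardstick only, since the article sets no between-arm difference or margin. For a comparability aim, the interval half-width (2.17 against 2.02 points) is the more relevant measure. The change is worth making because it is nearly free.

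**What to change.** In Section 4.1, for the randomised arm contrast on each questionnaire:

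1. Name the arm difference at the end of treatment as the tested contrast.
2. Fit this contrast without care level.
3. Use baseline in one of two ways. Either keep it in the outcome vector and constrain the two arms to a common baseline mean, or take only post-baseline scores as outcomes, with baseline and baseline-by-time as covariates.
4. Keep the arm × care level × time model and the demographic interaction models as descriptive or exploratory analyses.

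Adding sex, gender, age and income together as main effects is optional good practice. Little gain should be expected, and a few degrees of freedom are spent.

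The cost is analysis wording and a few lines of code, with no new data and no more participants. The covariate version drops anyone with no post-baseline score, which here means those who leave before the midway questionnaire; the constrained version keeps them. With 45% completion expected, that favours the constrained version.

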#### Treatment arm 1: healthcare team allocation

3.3.1

Allocation of treatment intensity by the multi-professional healthcare team will be based on the following criteria:

The severity of symptoms/disability (DSM-5 criteria).Mental health factors (prior treatments and responses, current and past psychotic/manic episodes, current and past suicidal/homicidal ideation/attempts, family mental health history, past psychiatric history, and hospital admissions).Medical factors (current medical conditions and medications, personal and family medical history).Social factors (support system and living situation, and occupational, social, and personal functional impairment).

To assess the severity of MDD symptoms and the functional impairments, participants will complete the PHQ-9 and Sheehan Disability Scale (SDS) (42, 43) before the assessment appointment. The trained research assistant on the multidisciplinary team will conduct the assessment appointment and will relay the information to the rest of the team later to deliberate on treatment intensity allocation. All assessments will occur virtually through phone and video calls. Together, the healthcare team will decide whether the participant should be assigned to the e-CBT-only treatment, e-CBT treatment with weekly phone/video calls, or e-CBT treatment with pharmacotherapy. This process mimics the current triage process in clinical settings. To track cost-effectiveness, the trained research assistant will track the total duration of the individual assessment and team deliberation meetings for analysis of the total time commitment per patient.

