#### Treatment arm 2: AI algorithm allocation

3.3.2

Allocation of treatment intensity by the proposed AI algorithm will be based on the machine learning and natural language processing (NLP) of textual data provided by participants and their PHQ-9 score collected through a pre-treatment screening module called the Triage Module. This module, developed by the research team, (1) provides psychoeducation on the effects of psychotherapy, (2) collects PHQ-9 scores, and (3) asks participants six open-ended questions regarding their mental health history, their experiences with mental health disorders, and what mental health difficulties they are currently facing. Based on the participant’s answers to the open-ended questions, a variable called “Symptomatic Score” will be calculated using the NLP algorithm. If the PHQ-9 score < 19 and the Symptomatic Score > 0.75, the participant will be assigned to the e-CBT-only treatment group. However, if either the PHQ-9 score is >19 or the Symptomatic Score is <0.75, the participants will be assigned to the e-CBT treatment with weekly phone/video calls. If both scenarios occur and the PHQ-9 > 19 and Symptomatic Score < 0.75, then the participant will be assigned to the e-CBT treatment with pharmacotherapy. This NLP algorithm is patented by OPTT Inc. (International Patent System, PCT/US22/43514).

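### The level-by-time terms of the section 4.1 mixed model cannot be read as effects of care intensity, because level is not randomised and in Arm 2 is set partly by PHQ-9

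*Protocol article*

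**What the plan says.** Section 4.1 (Hypothesis 1) specifies a 2 x 3 x 3 "linear mixed-effects model for each questionnaire to compare clinical outcomes within and between groups and times". The factors are arm, care level and time (start, midway, end), so the start score is part of the outcome vector. The only further factors named are sex, gender, age and income, brought in through separate demographic models. Neither baseline PHQ-9 nor the Symptomatic Score is a covariate.

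Section 3.3.2 defines care level in Arm 2 by a rule. The lowest level needs PHQ-9 below 19 and a Symptomatic Score above 0.75. The middle level needs one of the two opposite conditions. The highest applies "If both scenarios occur and the PHQ-9 > 19 and Symptomatic Score < 0.75". Section 3.3.1 leaves the Arm 1 level to the team, which weighs symptom severity, psychiatric history, medical factors and social factors. To inform severity, "participants will complete the PHQ-9 and Sheehan Disability Scale (SDS") ahead of the intake interview.

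Section 2 puts the effectiveness of the stratified care model in the primary objective, next to the comparison of AI with the healthcare team. Nothing in the article calls the level comparison descriptive or mentions regression to the mean.

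**The concern.** In Arm 2 the variable that helps to form the groups is also, or is closely related to, the first outcome measurement. People selected for a high PHQ-9 tend to score lower when measured again, whatever care they receive, and people selected for a low score fall less. Equal mean change across levels is therefore not what one expects when care intensity has no effect. The allocation criteria are also meant to be prognostic, so levels differ in expected course for reasons other than the care given.

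A significant level-by-time result on PHQ-9 could thus come from the selection rule alone. If the arms select on PHQ-9 to different degrees, the arm-by-level-by-time term is affected too, and an apparent difference between AI and team within levels could arise in the same way.

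**Working it through.** **The plan's own figures.** Section 3.10 states that "the average PHQ-9 score changed from 16.2 before e-CBT to 11.48 after 12 sessions of e-CBT" ("joint standard deviation; SD = 5.45") and that "the effect size (Hedges’ G) is equal to 0.86". The ratio (16.2 − 11.48)/5.45 = 4.72/5.45 = 0.866 agrees. "Given the effect size and a power of 0.8, we would need 14 participants", it continues. An exact two-sided paired t-test at 0.86 gives 13 (power 81.2%), and 14 gives 84.5%. Then 14/0.45 = 31.1, and 31 × 6 = 186. These reproduce closely enough to serve as inputs.

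**Inputs from the article.** Means 16.2 and 11.48, SD 5.45, N = 186, 45% with an end score, the cut at 19. All analyses "will consider a significance level of 0.05 and 95% confidence intervals" (taken as two-sided). Level shares in the 190-person verification sample of section 3.3.2 are 32.63%, 52.63% and 14.74%, taking its third group as the highest level.

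**Assumptions, not in the article.** Before-after correlation r = 0.3 to 0.7, 65% with a midway score, Symptomatic Score independent of PHQ-9 and without prognostic value, normally distributed scores.

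**Share with a low Symptomatic Score.** Let p be the probability of a low score and q that of a high PHQ-9. Under independence pq = 0.1474 and (1 − p)(1 − q) = 0.3263, so p + q = 1 + 0.1474 − 0.3263 = 0.8211. The roots are 0.556 and 0.265; p is taken as 0.556. With P(PHQ-9 > 19) = 1 − Φ(2.8/5.45) = 0.304, the simulated shares are about 31/52/17%.

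**Expected falls with no effect of level.** Mean baseline PHQ-9 by level is about 13.48, 15.79 and 22.48. With equal SDs the follow-up regresses on baseline with slope r, so

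fall in level k = 4.72 + (1 − r)(baseline mean in k − 16.2).

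At r = 0.5: lowest 4.72 + 0.5 × (−2.72) = 3.36; highest 4.72 + 0.5 × 6.28 = 7.86. The gap is 4.5 points, against an average fall of 4.72. In general the gap is (22.48 − 13.48)(1 − r) = 9.0(1 − r): 6.3, 4.5, 2.7 and 0.9 points at r = 0.3, 0.5, 0.7 and 0.9.

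**Level-by-time test in the 2 x 3 x 3 random-intercept model**, nominal 5%, 1,000 null trials per cell:

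| Arm 1 levels | r = 0.3 | r = 0.5 | r = 0.7 |
|---|---|---|---|
| follow the Arm 2 rule | 95% | 83% | 56% |
| severity rating correlated 0.6 with PHQ-9 | 81% | 60% | 37% |
| unrelated to PHQ-9 | 36% | 25% | 16% |

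With levels assigned at random in both arms (r = 0.5) the rate is 5.5%. Monte Carlo error is at most √(0.5 × 0.5/1000) = 1.6 percentage points. A simpler test on completers' change scores gives 42% to 78%, 26% to 58% and 13% to 23% in the three rows. Other runs of that test under similar assumptions, with levels unrelated to PHQ-9 in Arm 1, go down to 12%.

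**Other terms.** Arm-by-time rejects in about 6% in the first two rows and 7% to 9% in the third. Arm-by-level-by-time rejects in about 6%, 7% to 9%, and 16% to 36%.

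**Separate triage PHQ-9.** Suppose the triage score is a different administration, correlated 0.9 or 0.8 with the analysed baseline and related to follow-up only through it. The first-row rate at r = 0.5 falls from 83% to 74% or 61%. A completers' change-score simulation at retest correlation 0.8 gave 43% (r = 0.5, team follows PHQ-9) and 10% (r = 0.7, team ignores it).

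**Adjustment.** The end score adjusted for baseline PHQ-9 rejects in 4.5% to 6.0% in the scenarios of the table. Once the Symptomatic Score is made prognostic, baseline PHQ-9 alone leaves 11% to 67%, against 4% to 6% with both PHQ-9 and the score as covariates.

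**The case against.** The three hypotheses all concern AI versus team, and section 4.1 opens with that comparison. None says that calls or pharmacotherapy give a larger improvement than e-CBT alone. The sample size rests on a paired before-after test within each group, which needs no contrast between levels. A reader might infer that the protocol plans to claim an effect of care intensity from the level-by-time term; it does not say so. What remains is that the model makes the comparison, the primary objective includes the stratified care model, and nothing limits how the term may be read.

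A reader might also infer that levels in both arms are cut on the analysed baseline score. The documents do not support that. The cut is explicit only in Arm 2, and there jointly with the Symptomatic Score. In Arm 1, PHQ-9 is one input among several. The article does not say that the triage, pre-interview and analysed baseline PHQ-9 are a single administration.

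The size depends on correlations that the article does not give. The bias shrinks as r approaches 1, and would vanish if the triage score were no more related to baseline than to later scores. These points widen the range; they do not remove the fault.

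A statistical analysis plan could add a caveat, but the article itself already fixes the time points and the added factors.

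**Conclusion.** The concern holds for the care-level part of the PHQ-9 analysis. With no effect of level and r between 0.3 and 0.7, the level-by-time test rejects in roughly 35% to 95% of trials if Arm 1 levels also follow PHQ-9, and roughly 12% to 36% if they do not. This rests on the section 3.10 means and SD, the Arm 2 rule as written and the assumptions listed, including that triage and baseline share one PHQ-9. Separate administrations or a higher correlation give less inflation. The effect is weaker for QIDS and AQoL-8D and was not quantified for them.

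Two stronger conclusions are not supported. The randomised AI-versus-team comparison over time is not undermined: its rejection rate stays at about 6%, or 7% to 9% at worst. Nor does adjusting for baseline PHQ-9 alone settle the matter. Section 3.3.2 reports that the algorithm's groups differed in completion and final PHQ-9 under the same e-CBT, so confounding by indication is to be expected.

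**What to change.** In section 4.1, state that care-level contrasts are non-randomised and descriptive in both arms, and that unadjusted level-by-time and arm-by-level-by-time terms will not be interpreted as effects of care intensity.

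Where levels are compared, take the start score out of the outcome vector. Model the post-baseline scores with baseline PHQ-9, the questionnaire's own baseline and the Symptomatic Score as covariates, plus SDS for Arm 1. Align the sentence in section 3.3 that restricts which assessment data are analysed in each arm, because using the Symptomatic Score in Arm 1 would conflict with it.

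The cost is wording. All participants complete both the intake assessment and the Triage Module, and SDS is a baseline measure, so no new data are needed.

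The limits should be stated too. In Arm 2 level is fully determined by PHQ-9 and the Symptomatic Score, so levels do not overlap on the two covariates jointly and adjusted contrasts depend on the fitted form at the cut-offs. They will also be imprecise: 14.74% of 93 is about 14 people in the highest level, and 45% of those is about 6 end scores. In Arm 1 the covariates capture clinical judgement only in part.
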